### 9.9.2 Inferential methods

Null hypothesis:

There's no difference between the effects of NeoRecormon and placebo on cycling performance

parameters.

#### **9.10 Exploratory analyses and deviations**

Exploratory data-driven analyses can be performed with the caveat that any statistical inference will not have any confirmatory value. Deviations from the original statistical plan will be documented in the clinical study report.

#### **9.11 Interim analyses**

No interim analysis is planned.

---

## **10 GOOD CLINICAL PRACTICE, ETHICS AND ADMINISTRATIVE PROCEDURES**

### **10.1 Good clinical practice**

#### **10.1.1 Ethics and good clinical practice**

The investigator will ensure that this study is conducted in full compliance with the protocol, the principles of the Declaration of Helsinki, ICH GCP guidelines, and with the laws and regulations of the country in which the clinical research is conducted.

#### **10.1.2 Ethics committee / institutional review board**

The investigator will submit this protocol and any related documents to an Ethics Committee (EC) and the Competent Authority (CA). Approval from the EC and the statement of no objection from the CA must be obtained before starting the study, and should be documented in a dated letter/email to the investigator, clearly identifying the trial, the documents reviewed and the date of approval. A list of EC members must be provided, including the functions of these members. If study staff were present, it must be clear that none of these persons voted.

Modifications made to the protocol after receipt of the EC approval must also be submitted as amendments by the investigator to the EC in accordance with local procedures and regulations.

#### **10.1.3 Informed consent**

It is the responsibility of the investigator to obtain written informed consent from each individual participating in this study after adequate explanation of the aims, methods, objectives and potential hazards of the study. The investigator must also explain to the subjects that they are completely free to refuse to enter the study or to withdraw from it at any time for any reason.

The Informed Consent and Subject Information will be provided in dutch.

#### **10.1.4 Insurance**

The investigator has a liability insurance which is in accordance with article 7, subsection 6 of the WMO.

The investigator has an insurance which is in accordance with the legal requirements in the Netherlands (Article 7 WMO and the Measure regarding Compulsory Insurance for Clinical Research in Humans of 23rd June 2003). This insurance provides cover for damage to research subjects through injury or death caused by the study.

- € 650,000.- (i.e., six hundred and fifty thousand Euro) for death or injury for each subject who participates in the Research;
- € 5,000,000.- (i.e., five million Euro) for death or injury for all subjects who participate in the Research;
- € 7,500,000.- (i.e., seven million five hundred thousand Euro) for the total damage incurred by the organisation for all damage disclosed by scientific research for the Sponsor as 'verrichter' in the meaning of said Act in each year of insurance coverage.

The insurance applies to the damage that becomes apparent during the study or within 4 years after the end of the study.

### **10.2 Study funding**

CHDR is the sponsor of the study and is funding the study.

### **10.3 Data handling and record keeping**

#### **10.3.1 Data collection**

Data will be recorded on paper and/or electronic data collection forms and will be entered after quality control in a Promasys database for subsequent tabulation and statistical analysis. The data will be handled confidentially and if possible anonymously.

A Subject Screening and Enrolment Log will be completed for all eligible or non-eligible subjects with the reasons for exclusion.

#### **10.3.2 Database management and quality control**

A quality control check will be done by CHDR staff using data entry progress checks and database listings (blind data review). Errors with obvious corrections will be corrected before database lock. Results of computer tests and electronically captured questionnaires, clinical laboratory and efficacy analyses will be sent electronically to CHDR and loaded into the database.

After the database has been declared complete and accurate, the database will be locked. Any changes to the database after that time can only be made by joint written agreement between the investigator and the statistician.

#### **10.4 Access to source data and documents**

All study data will be handled confidentially. The investigator will retain the originals of all source documents generated at CHDR for a period of 2 years after the report of the study has been finalised, after which all study-related documents will be archived (at a minimum) on micro-film which will be kept according to GCP regulations.

The investigator will permit trial-related monitoring, audits, EC review and regulatory inspections, providing direct access to source data and documents.

#### **10.5 Quality control and quality assurance**

This study will be conducted according to applicable Standard Operating Procedures (SOPs). Quality assurance will be performed under the responsibility of CHDR's Quality Assurance manager.

##### **10.5.1 Monitoring**

An initiation visit will be performed before the first subject is included. Monitoring visits and contacts will occur at regular intervals thereafter, according to a frequency defined in the study-specific monitoring plan. A close-out visit will be performed after study closure.

#### **10.6 Protocol amendments**

Any change to a protocol has to be considered as an amendment.

##### **10.6.1 Non-substantial amendment**

Administrative or logistical minor changes require a non-substantial amendment. Such changes include but are not limited to changes in study staff or contact details or minor changes in the packaging or labelling of study drug. Non-substantial amendments will be approved (signed) by the investigator(s) and will be recorded and filed by the investigator but will not be notified to the EC and the CA.

The implementation of a non-substantial amendment can be done without notification to the appropriate EC or CA. It does not require their approval.

The following amendments will be regarded as non-substantial:

- change in timing of the samples;
- changes in assay-type and / or institution where an assay will be performed, provided that validated assays will be used;
- editorial changes to the volunteer information sheets;
- determination of additional parameters in already collected materials, which are in agreement with the study objectives and do not provide prognostic or genetic information;
- other statistical analyses than described in the protocol.

##### **10.6.2 Substantial amendment**

Significant changes require a substantial amendment. Significant changes include but are not limited to: new data affecting the safety of subjects, change of the objectives/endpoints of the study,

eligibility criteria, dose regimen, study assessments/procedures, treatment or study duration, with or without the need to modify the core Subject Information and Informed Consent Form.

Substantial amendments are to be approved by the appropriate EC and the CA will need to provide a 'no grounds for non-acceptance' notification prior to the implementation of the substantial amendment.

### ***Urgent amendment***

An urgent amendment might become necessary to preserve the safety of the subjects included in the study. The requirements for approval should in no way prevent any immediate action being taken by the investigators in the best interests of the subjects. Therefore, if deemed necessary, an investigator can implement an immediate change to the protocol for safety reasons. This means that, exceptionally, the implementation of urgent amendments will occur before submission to and approval by the EC(s) and CA.

### **10.7 End of study report**

The investigator will notify the EC and the CA of the end of the study within a period of 90 days. The end of the study is defined as the last subject's last visit.

In case the study is ended prematurely, the investigator will notify the EC and the CA within 15 days, including the reasons for the premature termination.

Within one year after the end of the study, the investigator will submit a final study report with the results of the study, including any publications/abstracts of the study, to the EC and the CA. The principal investigator will be the signatories for the study report.

### **10.8 Public disclosure and publication policy**

In accordance with standard editorial and ethical practice, the results of the study will be published. The authorship guidelines of the Vancouver Protocol will be followed regarding co-authorship.

The principal investigator will have the opportunity to review the analysis of the data and to discuss the interpretation of the study results prior to publication.

---

 <http://www.icmje.org/>

## **11 STRUCTURED RISK ANALYSIS**

Please refer to the respective Summary of Product Characteristics (SmPC, see appendix 1) and the European Public Assessment Report (EPAR, see appendix 3).

## **13 APPENDIX 1 – SUMMARY OF PRODUCT CHARACTERISTICS – ENGLISH VERSION**

## **14 APPENDIX 2 – SUMMARY OF PRODUCT CHARACTERISTICS – DUTCH VERSION**

## **15 APPENDIX 3 – EUROPEAN PUBLIC ASSESSMENT REPORT**

## 16 APPENDIX 4 – SCREENING: QUESTIONNAIRE SPORT ACTIVITIES

Sport activities in the past 3 years:

|   | Type of sport | Times a week | Distance and duration per training/competition | Mean velocity | Since when |
|---|---------------|--------------|------------------------------------------------|---------------|------------|
| 1 |               |              |                                                |               |            |
| 2 |               |              |                                                |               |            |
| 3 |               |              |                                                |               |            |
| 4 |               |              |                                                |               |            |
| 5 |               |              |                                                |               |            |

Sport activities in the past 6 weeks:

|   | Type of sport | Times a week | Distance and duration per training/competition | Mean velocity | Since when |
|---|---------------|--------------|------------------------------------------------|---------------|------------|
| 1 |               |              |                                                |               |            |
| 2 |               |              |                                                |               |            |
| 3 |               |              |                                                |               |            |
| 4 |               |              |                                                |               |            |
| 5 |               |              |                                                |               |            |

Dutch:

Sport activiteiten in de afgelopen 3 jaar:

|   | Type sport | Aantal keer per week | Afstand en duur van training/competitie | Gemiddelde snelheid (km/u) | Sinds wanneer |
|---|------------|----------------------|-----------------------------------------|----------------------------|---------------|
| 1 |            |                      |                                         |                            |               |
| 2 |            |                      |                                         |                            |               |
| 3 |            |                      |                                         |                            |               |
| 4 |            |                      |                                         |                            |               |
| 5 |            |                      |                                         |                            |               |

Sport activiteiten in de afgelopen 6 weken:

|   | Type sport | Aantal
keer per
week | Afstand en duur van
training/competitie | Gemiddelde
snelheid (km/u) | Sinds
wanneer |
|---|------------|----------------------------|--------------------------------------------|-------------------------------|------------------|
| 1 |            |                            |                                            |                               |                  |
| 2 |            |                            |                                            |                               |                  |
| 3 |            |                            |                                            |                               |                  |
| 4 |            |                            |                                            |                               |                  |
| 5 |            |                            |                                            |                               |                  |

## **17 APPENDIX 5 – EXERCISE TEST**

During this study the exercise tests will be performed on a cycle ergometer.

The subjects will cycle at a self-selected pedal rate (between 70 and 90 rpm) and this pedal rate along with the saddle and handlebar heights will be recorded and reproduced in subsequent tests.

All subjects will breathe through a facemask that is connected to an oxymeter to collect inspired and expired gasses for analyzing oxygen consumption, carbon dioxide production, minute ventilation, tidal volume and breathing frequency. Before each test, the oxymeter will be calibrated to ensure valid measurements. Blood pressure and heart rate will also be monitored during the tests. The blood pressure and heart rate measuring devices, cycle ergometer and oxymeter will be connected to a computer to measure and analyse all data.

### **18.1 Ramp exercise test**

#### **Protocol**

A ramp protocol will be followed until exhaustion, which will take approximately 1 hour. The details of the ramp exercise test will be described in the exercise test manual.

### **18.2 Time to exhaustion test**

#### **Protocol**

This exercise test will be performed according to a protocol looking at performance at submaximal intensity. It will last approximately 1 hour. The details of time to exhaustion test will be described in the exercise test manual.

### **18.3 Statistics**

All data will be presented as means  $\pm$  SD (or standard error). First, a two-way factor (group versus respectively  $V_{O_2}$ ,  $V_{O_2}/kg$ ,  $\%V_{O_{2max}}$ ,  $W$  and  $W/kg$ ) ANOVA with repeated measures will be performed to determine if an interactive effect exists between both groups and mentioned parameters. These parameters will be analyzed at VT1, VT2 and maximal intensity. The ANOVA will be conducted to determine whether the factor group will significantly influence these physiological parameters. When a significant F-ratio is detected, comparisons for unpaired data will be performed (Student's t-tests) to locate the differences (2-tailed). Maximal lactate values between both groups will also be compared using an unpaired Student's t-test.  $V_{O_2}$  at the ventilatory and lactate thresholds will be used to compare both thresholds by using a paired Student's t-test. Statistical significance will be set at  $P < 0.05$ .

## 18 APPENDIX 6 – COMPETITION

Subjects will climb the Mont Ventoux in an open course via Bédoin after a 150km closed course. A blood sample of each subject will be collected in Bédoin (at the end of the closed course) and at the finish. A power meter will be incorporated into each bike.

[figure not shown]

Figure 2. Detailed description of the Mont Ventoux climb via Bédoin.

| BÉDOIN              |         |
|---------------------|---------|
| WIKI                | Bédoin  |
| STARTING ALTITUDE   | 290 m   |
| FINISHING ALTITUDE  | 1912 m  |
| LENGTH              | 21.5 km |
| DIFFERENCE IL LEVEL | 1620 m  |
| AVERAGE GRADIENT    | 7.5 %   |
| MAXIMUM GRADIENT    | 12.5 %  |

**Figure 3.** Characteristics of the Mont Ventoux climb via Bédoin.

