#### 1.4.9.2 Power calculation based on $P_{max}/kg$

A better endpoint would be power output per kilogram (P/kg) at a submaximal level, such as 80% of  $V_{O2,max}$ . Unfortunately no studies have been performed using this endpoint, so the effect of rHuEPO on P/kg at 80%  $V_{O2,max}$  is still unknown. The mean P/kg at 80%  $V_{O2,max}$  of 11 male professional cyclists however, is 5.2 W/kg with a standard deviation of 0.199.  Using a sample size of 22 (including 10% attrition rate) and a two-tailed t-test with a 0.05 two sided significance level a difference of 0.172 W/kg can be detected with a power of 80%. This difference would mean that a professional cyclist weighing 75 kg would go from an average of 390 W at 80%  $V_{O2,max}$  to 402.9 W. On a racing bike weighing 9 kg sitting in racing position at 25 degrees Celsius, this would produce a speed of 43.80 km/h and 44.32 km/h respectively (calculated from <http://bikecalculator.com>). In a flat terrain of 40 km this would result in a finish time of 54 min 48 sec and 54 min 09 sec, a difference of 39 seconds, which is very relevant in a race like to Tour the France.

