#### *Exercise tests*

All subjects will breathe during the exercise test through a facemask that will be connected to an oxymeter to collect inspired and expired gasses for analyzing:

- Oxygen consumption,  $V_{O_2}$  (L/min)
- Carbon dioxide production,  $V_{CO_2}$  (L/min)
- Respiratory minute ventilation,  $V_E$  (L/min)
- Tidal volume,  $V_t$  (L)
- Respiratory frequency,  $R_f$
- Maximal oxygen consumption,  $V_{O_{2,max}}$  ( $ml\ kg^{-1}\ min^{-1}$ )

During the exercise tests blood will be collected at predetermined stages to measure:

- Lactate levels
- Tissue plasminogen activator
- Creatinine phosphokinase
- C-reactive protein levels

$V_{O_2}$  and  $V_{CO_2}$  will be used to calculate:

- Ventilatory equivalent for oxygen ( $V_E/V_{O_2}$ ),  $eqV_{O_2}$
- Ventilatory equivalent for carbon dioxide ( $V_E/V_{CO_2}$ ),  $eqV_{CO_2}$

these values will be used to determine:

- Ventilatory threshold 1, VT1
- Ventilatory threshold 2, VT2

Physiological parameters that will be determined at VT1 and VT2:

- Oxygen consumption,  $V_{O_2}$  (L/min)
- Oxygen consumption per kg,  $V_{O_2}$  (L/min/kg)
- Percentage of maximal oxygen consumption,  $\%V_{O_{2,max}}$  (L/min)
- Power output,  $P$  (J/s)
- Power output per kg,  $P$  (J/s/kg)

Physiological parameters that will be determined at maximal effort:

- Maximal oxygen consumption,  $V_{O_{2,max}}$  (L/min)
- Maximal oxygen consumption per kg,  $V_{O_{2,max}}$  (L/min/kg)
- Maximal power output,  $P_{max}$  (J/s)
- Maximal power output per kg,  $P_{max}$  (J/s/kg)
- Lactate values

Other determinations:

- Lactate threshold 1, LT1
- Lactate threshold 2, LT2
- Cycling economy, CE ( $W\ L^{-1}\ min^{-1}$ )
- Gross efficiency, GE (%)

- Heart rate (bpm)
- Systolic blood pressure (mmHg)
- Diastolic blood pressure (mmHg)

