### *Competition*

Exercise parameters that will be measured and calculated during the competition:

- Result in the race
- Total time of the race
- Power (W)
- Heart rate (bpm)
- Systolic blood pressure (mmHg)
- Diastolic blood pressure (mmHg)

Before and after the competition blood will be collected to determine if certain protein concentrations are influenced by NeoRecormon such as:

- Lactate
- Tissue plasminogen activator
- Creatinine phosphokinase
- C-reactive protein
- Coagulation and activation markers (D-Dimer, F1+2, p-Selectin, e-Selectin, ThromboxaneB2, bTG, PF4, thrombomodulin)

In urine:

- Proteinuria

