#### 7.2.3 Weight and height

Weight (kg) will be recorded at screening, before each exercise test and the follow-up visit or upon early termination. Height (cm) will be recorded and body mass index (BMI) calculated at screening.

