## 9.9 Efficacy endpoints

### 9.9.1 Efficacy

The final analysis will be preceded by a blind data review which consists of individual graphs per visit by time of all efficacy measurements by time. The graphs will be used to detect outliers and measurements unsuitable for analysis. The efficacy parameters will be listed by treatment, subject, visit and time. Individual graphs by time will be generated.

All measured PD endpoints will be summarised (n, mean, SD, SEM, median, Min and Max values) by treatment and time, and will also be presented graphically as mean over time, with standard deviation as error bars. All efficacy endpoints will be summarised (mean, SD, SEM, median, Min and Max values) by treatment, and will also be presented graphically as mean in a bargraph, with standard deviation as error bars.

Parameters will initially be analyzed without transformation, but if the data suggest otherwise, log-transformation may be applied. Log-transformed parameters will be back-transformed after analysis where the results may be interpreted as percentage change.

To establish whether significant treatment effects can be detected on the measured efficacy parameters, each parameter that is measured repeatedly will be analyzed with a mixed model analysis of covariance (ANCOVA) with treatment, time and treatment by time as fixed factors and subject, subject by treatment and subject by time as random factors and the (average) baseline measurement as covariate. Parameters that are only measured at baseline and at the end of the treatment phase will be analysed with a one-way ANCOVA with treatment and baseline as covariate.

Single measured efficacy parameters will be analyzed with an unpaired t-test.

The Kenward-Roger approximation will be used to estimate denominator degrees of freedom and model parameters will be estimated using the restricted maximum likelihood method.

The general treatment effect and specific contrasts will be reported with the estimated difference and the 95% confidence interval, the least square mean estimates and the p-value. Graphs of the Least Squares Means (LSM) estimates over time by treatment will be presented with 95% confidence intervals as error bars, as well as change from baseline LSM estimates.

The following contrasts will be calculated within the model:

- NeoRecormon - Placebo

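### Race power is listed only in absolute watts and compared without adjustment for body size, so body-mass differences add noise that can hide a treatment effect

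*Protocol*

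**What the plan says.** - **Course.** Protocol Appendix 6: "Subjects will climb the Mont Ventoux in an open course via Bédoin after a 150km closed course". Its table gives a climb of 21.5 km, 1620 m of height gain and a 7.5% average gradient. Each bike carries a power meter.
- **Race outcomes.** The competition list in section 6.1 contains "Result in the race", "Total time of the race", power in watts, heart rate and blood pressure. It has no per-kg power.
- **Laboratory outcomes.** The exercise-test list in the same section gives power in both forms at VT1, at VT2 and at maximal effort, for example "Maximal power output per kg". The statistics paragraph of Appendix 5 also names both W and W/kg.
- **Analysis.** Section 9.9.1: "Single measured efficacy parameters will be analyzed with an unpaired t-test". There is one race and no baseline race, so this rule covers race power.
- **Allocation.** Section 5.6.1 blocks by age group only, so nothing in the design balances body mass.
- **Weight data.** Section 7.2.3: "Weight (kg) will be recorded at screening, before each exercise test".

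**The concern.** On a sustained 7.5% gradient a heavier rider must produce more watts than a lighter one to hold the same speed. Part of the spread in race watts between riders is therefore body size, which has nothing to do with the drug. An unadjusted t-test leaves that spread in its standard error.

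The protocol uses W/kg elsewhere: in the entry criterion, in the laboratory outcomes and in its second power calculation. The race is the only setting where the per-kg form is dropped. At stake is an uninformative null result on race power, one of the more direct measures of individual output in the secondary race objective.

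**Working it through.** **1. The plan's own figure.** Section 1.4.9.2 states that P/kg "is 5.2 W/kg with a standard deviation of 0.199". It gives a detectable difference of 0.172 W/kg with 22 per arm, 80% power and two-sided alpha of 0.05. A two-sample t-test calculation returns 0.1721 W/kg, so the figure reproduces. The ratio is 0.172/0.199 = 0.864 SD. At 75 kg the effect is 0.172 × 75 = 12.9 W (390 to 402.9 W), or 0.172/5.2 = 3.3%. The gradient also checks: 1620/21500 = 7.5%.

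**2. Variance of watts against W/kg, independence assumed.** The documents give no spread of body mass. Assume a coefficient of variation (CV) *a* for body mass (10%, range 6-12%) and *b* for W/kg (10%, range 8-12%).

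CV of watts = √(a² + b² + a²b²)

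| a | b | CV of watts | Variance ratio, W to W/kg |
|---|---|---|---|
| 10% | 10% | √0.0201 = 14.2% | 0.0201/0.0100 = 2.0 |
| 6% | 12% | √0.01805 = 13.4% | 0.01805/0.0144 = 1.25 |
| 12% | 8% | √0.02089 = 14.5% | 0.02089/0.0064 = 3.3 |

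In the central case the detectable difference is 0.864 × 14.2% = 12.3% in watts against 0.864 × 10% = 8.6% in W/kg.

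**3. Dropping independence.** With correlation ρ between body mass and W/kg, on the log scale:

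variance ratio = 1 + (a² + 2ρab)/b²

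This equals 1 at ρ = -a/(2b). Break-even is -0.5 for CVs of 10% and 10%, and -0.25 for 6% and 12%. Below it, the plain ratio W/kg is the noisier of the two.

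**4. Weight as covariate instead.** On the log scale, watts regressed on body mass leave residual variance b²(1 - ρ²). At CVs of 10% and 10% and ρ = -0.5, unadjusted watts and W/kg both have variance b², while the adjusted analysis has 0.75b². It therefore still gains where the ratio does not.

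**5. Power with the protocol's SD.** Take SD 0.199 W/kg, mean 5.2 W/kg, 75 kg, 22 per arm, an effect of 12.9 W and independence.

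SD of watts = √[(75 × 0.199)² + (5.2·SDm)² + (0.199·SDm)²], where SDm is the assumed body-mass SD

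| Body-mass SD (assumed) | SD of watts | t-test power in watts |
|---|---|---|
| 4 kg | 25.6 W | 37% |
| 6 kg | 34.6 W | 23% |
| 8 kg | 44.2 W | 16% |
| 10 kg | 54.1 W | 12% |

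Power in W/kg is 80%. Simulated power for watts with weight as covariate is about 78%. This is the favourable extreme, because 0.199 is the laboratory SD of 11 professionals, a CV of 0.199/5.2 = 3.8%. With an assumed SD of 0.4 W/kg, power is 29% in W/kg against 11-16% in watts. With the 10% CVs of step 2, a 3.3% effect has about 19% power in W/kg and 12% in watts. The direction holds, but the fix would not by itself make so small an effect detectable.

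**6. False positives.** With no treatment effect, simulated type I error for the t-test on watts is 5.1-5.2% for body-mass SDs of 6, 8 and 10 kg, which is nominal. One standard error of chance imbalance in mean weight is SDm × √(2/22) = 1.8 to 3.0 kg for SDs of 6-10 kg. At 5.2 W/kg that is 9 to 16 W, the same order as the 12.9 W effect.

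**The case against.** - **This belongs to the SAP.** Section 9.1 leaves derivation algorithms to the SAP, which is not at hand, and nothing forbids deriving W/kg there. This stands in part. But the protocol names the unit of race power and the test for it, and it names both units for the laboratory tests. That is a stated choice, although an easily repaired one.
- **The race does not rest on watts.** Race result and total time are listed too, and both already reflect the effect of body mass on climbing. This stands. A reader might infer that the whole race objective is compromised; the documents do not support that. Total time does include the 150 km before the climb, so it does not replace a power measure on the climb.
- **The preference for P/kg is not about race watts.** Section 1.4.9.2 says "A better endpoint would be power output per kilogram (P/kg) at a submaximal level", but synopsis section 8.2 shows that the comparison is with VO2max, for sample size. Its speed example is on flat terrain. This stands, so the argument here rests on the laboratory lists and the climb.
- **Imbalance in weight could mimic a drug effect.** A reader might infer this from the 9 to 16 W figure. Allocation is randomised 1:1, so imbalance is chance. It can move the estimate in one trial, but the t-test's standard error already contains that spread, and the error rate stays at 5%.
- **The gain is assumed.** Body-mass spread, W/kg spread and independence are not in the documents. This stands, and the gain from the plain ratio can vanish or reverse.

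**Conclusion.** The point holds as a loss of precision in one secondary outcome. Race power is fixed in watts and tested without adjustment for body size, so body-mass differences widen the comparison and can hide an effect. There is no systematic bias and no excess of false positives, and race result and total time are not touched by the choice of unit.

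If body mass and W/kg are independent, the variance of watts is about 1.25 to 3.3 times that of W/kg over the assumed CVs. The ratio falls to about 1 if heavier riders have clearly lower W/kg (correlation about -0.5 at CVs of 10% and 10%). The power contrast of 80% against 12-37% applies only with the professionals' laboratory SD and independence, and should not be read as the expected loss in this race. Priority is minor: the race objective is secondary and worded as exploratory.

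**What to change.** In the competition list of section 6.1, add mean race power per kg, for the whole race and for the climb from Bédoin to the summit. Use the weight recorded at the last ramp test. Keep absolute watts as a reported value.

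Alternatively or in addition, state in section 9.9.1 that race watts are analysed by ANCOVA with treatment and pre-treatment body weight. This does not depend on the independence assumption, so it is the safer choice if only one change is made. Either change should be fixed before unblinding.

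**Cost.** One derived variable or one covariate, with no new measurement. By section 3.1 the last ramp test is on days 53-56 and the race on days 57-60, so the weight is 57 - 56 = 1 to 60 - 53 = 7 days old. Section 10.6.2 counts a change of endpoints as a substantial amendment, whereas section 10.6.1 counts other statistical analyses as non-substantial. The covariate is therefore the lighter route administratively.
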